### Study population

The inclusion criteria concern men and women aged 40–75 years with T2DM, who indicate to be unsatisfied about their sexual function and want to talk about their sexual problem with their GP. In addition, participants have to be able to read, write, and understand the Dutch language, which is necessary for filling out the questionnaires and talking to their GP. Participation in other scientific studies that aim to improve one or more of our outcome measures will result in study exclusion.

### Recruitment

All potential participants will be notified about the start of the study through posters in the GP’s waiting room. In addition, the practice nurse can give written information about the study. Recruitment of eligible patients is performed by the GP’s practice nurse. Given the frequent three-monthly meetings this will efficiently fit in routine care. Patients will be unaware of the practice’s randomisation status.

The practice nurse will ask all patients with T2DM aged 40–75 years to fill out a short screener questionnaire for scientific research. We use the Brief Sexual Symptom Checklist for men (BSSC-M) and women (BSSC-W) to screen for sexual dysfunction and dissatisfaction about sexual function in primary care (Fig. 1 and 2) [43]. We have slightly modified this questionnaire by changing question 5 from ‘would you like to talk about it with your doctor’ to ‘would you like to talk about it with your GP’. In addition, we added a sixth question for patients who might want to talk about their problem with another GP than their own.

**Fig. 1 Fig1:**
[figure not shown]
The modified Brief Sexual Symptom Checklist for Men (BSSC-M)

**Fig. 2 Fig2:**
[figure not shown]
The modified Brief Sexual Symptom Checklist for Women (BSSC-W)

Based on the results of the screener, patients are eligible for study participation if they report 1) to be sexually dissatisfied, and 2) that they would like to talk about their sexual problem with the GP. The practice nurse will explain that a scientific study program is tested in this practice, and that the particular patient is eligible for participation. Participation implies that the patient will need to fill out three questionnaires in the coming 12 months.

After handing in the baseline questionnaire, the patient receives an information leaflet from the practice nurse on Diabetes and Sexuality. In the intervention group, the practice nurse will subsequently make an appointment with the GP for each patient to talk about sexual problems. Practice nurses in the control group do not automatically make an appointment with the GP for every patient. Instead, the practice nurse will ask whether the information leaflet was of sufficient help or whether the patient would like to have an appointment with his/her GP nevertheless.

The practice nurse will fill notify the researchers if a patient consented to participate. A non-response form is filled out for those patients who do not agree to fill out the screener and/or do not want to participate in our study. The form includes the patient’s gender, year of birth, and ability to speak/read Dutch.

### Training of practice nurses

All practice nurses will receive one training session. Intervention and control practices will be trained in separate sessions to prevent contamination. The first part of the training focuses on the effects of sexual dysfunction in T2DM and about discussing sexual issues in clinical practice. Suggestions for an appropriate attitude and skills needed for introducing sexual issues are explained. This part of the training is deemed necessary for optimal recruitment of patients.

The second part of the training focuses on recruitment of eligible patients for study participation, as described above. Practice nurses will be taught to explain the study purposes, handing out the screener questionnaire, processing the results from the screener, and recruiting eligible patients for study participation.

The practice nurses will be instructed to include at least three eligible men and three eligible women per practice. The steps of the recruitment process will be practiced and references to relevant literature for further reading will be provided. The training will be given by two skilled researchers. A questionnaire to measure the practice nurse’s knowledge and competence with discussing sexual problems in patients with T2DM will be administered before and 3–4 weeks after the training.

### Intervention development

During the first step of the model, Permission, the care provider invites the patient to talk about sexual health and sexuality. One way to do so is by asking certain ‘cue questions’, such as ‘I ask all my diabetes patients about their sexuality, is it okay if I ask these questions to you now?’ or ‘People with diabetes often have questions about how diabetes may affect their sex life. Is there anything you would like to ask me?’. Permission here refers to explicit permission-giving by the patient to talk about this (yes/no) with the care provider. On the other hand, Permission also refers to the normalisation of sexual problems by the care provider (implicit permission-giving) [44]. The second step, Limited Information, concerns providing general information, for example regarding the effect of diabetes on sexual function. The first two steps of the PLISSIT model focus on the invitation to the patient to talk about sexuality and on the normalisation of the sexual problem [45].

Compared to the previous steps, the care provider needs additional skill and knowledge to carry out the third step of the model, Specific Suggestions. In order to provide relevant suggestions, the care provider needs to understand the patient’s particular complaint, which may include taking a sexual history [45]. Examples of specific suggestions may include the use of lubricants, lifestyle changes, or medication adjustment. These suggestions are aimed to directly help the patient within a relatively short period of time [45].

Since most GPs will not be skilled enough to perform the fourth step of the model, Intensive Therapy, this step will almost always include referring the patient to specialised care. Step four may be applied to complex sexual problems or problems that were not efficiently helped in the previous steps. For example, referral to a sexologist or psychologist may be necessary in case of relationship problems or sexual abuse [44]. The PLISSIT model thus provides a framework for when referral is appropriate, but most importantly, the model aids the care provider with the discrimination between problems for which brief therapy will suffice (step 1–3) and problems needing intensive therapy (step 4) [45].

### Training of GPs in the intervention group

GPs in the intervention group will receive one training session regarding the application of the PLISSIT model. General information about sexual (dys)function and T2DM will be provided. Role-play will be used to help the GPs become aware of their attitudes towards sexual health and sexuality. After the exercise, attitude and skills needed for discussing sexual problems will be discussed. The training continues with a thorough explanation of the steps and the application of the PLISSIT model, including relevant examples for each stage of the model, which may include, but are not limited to:Permission: examples of certain ‘cue questions’ will be given. For instance, ‘I ask all my diabetes patients about their sexual health, it is not an easy subject to talk about, but we know that many diabetes patients suffer from sexual problems. Is it okay to talk with you about this now?’.Limited Information: explanation of normal sexual functioning; explanation of the association between T2DM and sexual problems; and providing adequate additional information choosing from a variety of available information leaflets regarding sexuality and chronic illness.Specific Suggestions: a training in taking a short sexual history with respect to the age, gender, ethnicity, and sexual orientation of the patient. In addition, multiple examples of ‘specific suggestions’ will be given, such as prescribing lubricants or phosphodiesterase-5 inhibitors, or providing (further) psycho-education on facilitating and impeding factors of sex.Intensive Therapy: explanation of when to refer to which specialist, e.g. sexologist, psychologist, or gynaecologist. An overview of the local referral possibilities will be handed out during the training.

It will be emphasised that GPs should apply the model geared to an individual’s problems and needs, and that, consequently, not all steps are necessary for every patient. The model should not be interpreted as a linear structure, but as a dynamic process of consultation, including, when necessary, returning to previous steps or skipping one [44]. During the training, the application of the PLISSIT model will be practiced based on a theoretical case. Afterwards, references to relevant literature for further reading will be provided.

An experienced GP who also works as a certified sexologist will train the GPs in the intervention group. A questionnaire to measure the GP’s knowledge and competence with discussing sexual problems in patients with T2DM will be administered before and 3–4 weeks after the training.

### Intervention

In the intervention group, a consultation with the GP is scheduled two weeks after the meeting with the practice nurse. The GP will discuss the patient’s sexual problems according to the steps of the PLISSIT model, as described previously. Only after permission is given (step 1), the intervention will continue. In case the patient doesn’t give permission, the GP will emphasise that the patient may always raise this issue at a later moment [44]. The following steps of the model will be addressed based on the patient’s needs, allowing the GP to return to previous steps or to skip steps not deemed necessary. Since the majority of the patients will be helped by discussing the first three steps of the PLISSIT model, most of the counselling will take place in one or two consultation(s). Multiple consultations are expected to be necessary for (more) complex sexual issues in step 3 and 4.

If the GP suspects the patient to express depressive symptoms during the PLISSIT consultation, the GP will treat first what he/she deems necessary. The patient will receive care conform the NHG guideline for depressive symptoms [46]. When depressive symptoms are treated first, the GP will make a PLISSIT appointment after a clinically relevant interval.

### Control group

GPs in the control group provide care as usual [21]. At present, apart from the NHG guideline about ED [47], no NHG guideline regarding male or female sexual dysfunction exists. The GP will provide usual care conform the NHG guideline on depressive symptoms when deemed necessary [46], as previously described in the intervention strategy paragraph.

In order to establish equal referral options for both study arms, GPs in control practices will receive the same overview of specialists to whom they may refer their patients for further treatment. By providing both groups with this map we can correct for the effect a referral may have on our outcomes.

### Data collection and outcome measures

The following outcome measures are included in the questionnaires.

#### Primary outcome measures

Sexual function will be assessed with the 19-item Female Sexual Function Index (FSFI) for women [48], and the 15-item International Index of Erectile Function (IIEF) for men [49]. Both questionnaires are widely used and have been well-validated [50–52]. Satisfaction with sexual function will be measured on a 10-point Visual Analogue Scale (VAS) scale: ‘how satisfied are you with your sexual functioning on a scale from 0 to 10?’, where 0 indicates being very unsatisfied and 10 indicates being very satisfied. Quality of life will be assessed with the brief, reliable, and valid Short Form-12 item survey (SF-12) [53–55].

#### Secondary outcome measures

The 9-item Patient Health Questionnaire (PHQ-9) will be used to measure depressive symptoms [56]. The PHQ-9 has been validated in several (clinical) populations, and has shown to have good reliability, and high sensitivity and specificity for depression in patients with T2DM [57, 58]. The revised version of the Female Sexual Distress Scale (FSDS) [59], the FSDS-Revised (FSDS-R) [60], will be used to examine sexual distress. Consistent with the FSDS, the FSDS-R showed good psychometric properties for assessing sexuality-related personal distress in women [52, 59, 60]. We will use the FSDS-R to assess sexual distress in women. In addition, for exploratory purposes, we will use the FSDS-R to assess sexual distress in men. The World Health Organisation-Five Well-Being Index (WHO-5) will be used to measure emotional well-being, which has shown good psychometric properties as a screener for depression in patients with type 1 and 2 diabetes [61–63]. Finally, patients’ treatment satisfaction will be examined in qualitative interviews.

#### Process analysis

To assess whether the study protocol was followed as intended, we ask all patients at three (T1) and 12 (T2) months follow-up whether they received the information leaflet on diabetes and sexuality from the Dutch Diabetes Association and whether they had a conversation with the GP about sexual problems. In addition, we will ask about the number of return visits regarding sexual problems, and whether the patient was referred to another health care provider for this sexual problem.

A second part of the process analysis concerns qualitative research. All patients will be asked whether they may be approached for a telephone interview during the study. We will perform a purposeful sampling approach, taking the patient’s age, gender, and sexual functioning into account. An estimate of 15–20 interviews is necessary 1) to assess whether the intervention or the control procedures were performed according to the study protocol; and 2) to examine treatment satisfaction. The interviewer will be unaware of the patients randomisation status and sexual functioning.

### Sample size

We decided to settle for a power to detect an improvement of 25 % in sexual functioning, 10 % in the control group and 35 % in the intervention group. We calculated that 65 participants per group would be needed, assuming a two-sided test at an alpha of 0.05 and a power of (1 − beta) 0.90. Due to cluster randomisation at GP level, the sample size needed to be inflated based on the formula of the Design Effect: 1 + (n-1)∙ICC with n as the mean cluster size and ICC as the Intracluster Correlation Coefficient [64]. We estimate to recruit six eligible patients per practice (n=6). An ICC of 0.05 was chosen to account for the clustering of patients within practices [64, 65]. The Design Effect was calculated as 1.25. In addition, we accounted for a 20 % dropout. A total of 195 patients are needed. We will therefore aim to recruit 200 patients from 34 general practices.

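### The stated requirement of 195 patients covers 16.7% dropout, not the planned 20%; the plan's own inputs give 204, with only a small effect on power

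*Protocol article*

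**What the plan says.** All the inputs are in the Sample size section of the protocol article. The effect to be detected is a proportion improved of "10 % in the control group and 35 % in the intervention group", "assuming a two-sided test at an alpha of 0.05 and a power of (1 − beta) 0.90". From this the authors find that "65 participants per group would be needed".

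The figure is then inflated for clustering. On cluster size the article says "We estimate to recruit six eligible patients per practice (n=6"), and on correlation "An ICC of 0.05 was chosen to account for the clustering of patients within practices". "The Design Effect was calculated as 1.25".

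An allowance for 20% dropout is added, but the article does not say how it was applied. The section ends with two totals: "A total of 195 patients are needed", and "We will therefore aim to recruit 200 patients from 34 general practices".

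**The concern.** The article gives every input and the result, so the chain can be checked directly, and its last step does not hold. An allowance for 20% dropout means that 80% of those recruited are expected to remain, so the number needed at follow-up has to be divided by 0.80. The published total is what results from adding 20% to that number instead, which protects against a smaller loss.

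The required sample size is the figure against which readers will later judge whether recruitment was sufficient. If 195 is taken as the requirement and dropout is the 20% planned for, the trial ends with fewer effective patients per group than the 65 the plan asks for. Rounding up to 200 narrows the gap but does not quite close it.

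**Working it through.** **Inputs (all from the Sample size section):** 10% vs 35%; two-sided alpha 0.05; power 0.90; 65 per group; six patients per practice; ICC 0.05; dropout 20%; stated total 195; target 200 from 34 practices.

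**1. Reproducing 65 per group.** With a mean proportion of 0.225 and a difference of 0.25, the usual pooled formula is

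n = [1.960 x sqrt(2 x 0.225 x 0.775) + 1.282 x sqrt(0.10 x 0.90 + 0.35 x 0.65)]² / 0.25² = 56.5, so 57.

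With a continuity correction,

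n' = (56.5 / 4) x [1 + sqrt(1 + 4 / (56.5 x 0.25))]² = 64.3, so 65.

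The plan's 65 is therefore the continuity-corrected figure.

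**2. Reproducing the design effect.** 1 + (6 - 1) x 0.05 = 1.25, as stated.

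**3. Patients needed at follow-up.** 2 x 65 x 1.25 = 162.5.

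**4. Reproducing 195.** 162.5 x 1.2 = 195.0 exactly. The loss that this covers is 1 - 162.5/195 = 16.7%.

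**5. Correct allowance for 20% loss.** 162.5 / 0.80 = 203.1, so 204 in total, or 102 per group. (Rounding up to whole patients per group at every step gives 206.) The stated 195 is 9 short, 4.4% of 204. The target of 200 is 4 short, 2% of 204, and covers a loss of 1 - 162.5/200 = 18.75%.

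**6. Effect on power.** After 20% loss, effective patients per group = N x 0.80 / 1.25 / 2. Power for 10% vs 35%, two-sided 0.05:

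| Recruited | Remaining | Effective per group | Power, continuity-corrected | Power, uncorrected z-test |
|---|---|---|---|---|
| 195 | 156 | 62.4 | 89.0% | 92.7% |
| 200 | 160 | 64.0 | 89.9% | 93.3% |
| 204 | 163.2 | 65.3 | 90.5% | 93.7% |

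Fisher's exact test, enumerated at whole numbers, has power 90.0% with 62 per group and 91.1% with 64 per group.

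**7. Practices.** 34 x 6 = 204, so the planned number of practices at the planned cluster size already supplies the corrected total.

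**The case against.** A reader might infer from the shortfall that neither 195 nor 200 gives the trial its stated 90% power. There are good reasons not to go that far.

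- **The deficit appears on one basis only.** Power falls below 90% only with the continuity correction, by 1.0 point at 195 and 0.1 point at 200. The uncorrected z-test and Fisher's exact test both reach 90% at either total.
- **The 65 already contains slack.** Without the continuity correction 57 per group would do. The Analyses section plans linear and logistic multilevel regression, not a continuity-corrected comparison of two proportions. Missing 65 by 1 to 2.6 effective patients therefore does not show that the planned analysis has less than 90% power.
- **The design effect is conservative.** It uses six patients per practice, although 20% are then assumed lost. With 6 x 0.80 = 4.8 analysed per practice, the same formula gives 1 + 3.8 x 0.05 = 1.19. At 1.19, 195 leaves 65.5 effective patients per group (continuity-corrected power 90.6%) and 200 leaves 67.2 (91.4%).
- **195 is not the recruitment target.** The target is 200. The section on training of practice nurses makes three men and three women the minimum for each practice, so 34 practices that meet the instruction reach at least 204.

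All four points stand as arguments about power and practical consequence. None of them rescues the total as written. The plan states a cluster size of six and a design effect of 1.25, never 1.19, and 195 is exactly 162.5 x 1.2. Nothing elsewhere in the article corrects the figure.

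**Conclusion.** The figure of 195 is wrong as written, and the error is minor. On the plan's own 65 per group, design effect of 1.25 and 20% dropout, the requirement is 204. The article does not describe how dropout was applied. That it was applied as a factor of 1.2 is inferred from the exact match.

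The documents do not support calling the trial materially underpowered. The largest loss, on the strictest basis and at a total that is not even the recruitment target, is about one percentage point. At the actual target it is about a tenth of a point.

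These power figures assume 20% loss spread evenly over the two groups, equal cluster sizes, and the ICC of 0.05 and response proportions as stated.

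**What to change.** Restate the requirement as 204 patients (102 per group), showing 130 x 1.25 / 0.80 = 203.1, and change the target of 200 to 204 so that it agrees with 34 practices of six patients. This costs two numbers in the text. It means four more patients than the present target, and no practice is added.

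If 195 or 200 is to be kept, state the dropout that it actually covers with a design effect of 1.25: 16.7% for 195, or 18.75% for 200.

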### Randomisation and blinding

An independent statistician will randomly allocate the participating general practices to either one of the study arms by means of block randomisation. Practices will be matched based on location and number of patients with T2DM per practice. In addition, when necessary, we will account for practice nurses who work in multiple general practices by matching those practices in one block to ensure that practice nurses that work in different participating practices have a similar allocation in each practice. Patients will be unaware of the randomisation status, as is the analyst during the data handling and data analysis; GPs and practice nurses cannot be blinded.

### Analyses

Since we have chosen a cluster-randomised design with repeated measurements, observations and patients within a certain cluster are more alike and thus correlate to each other. We will therefore use linear and logistic multilevel regression analyses to study the effects of our trial. Data will be analysed as intention-to-treat and differences in outcomes measures between the intervention and control group will be calculated with 95 % confidence intervals. Given that not every patient in the control group will have had an appointment with their GP, a sensitivity analysis will be conducted to compare patients who had an appointment with their GP in the intervention versus control group.

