## Background

Sexual problems are highly prevalent among patients with type 2 diabetes mellitus (T2DM) [1, 2].

Although prevalence rates vary widely between studies, patients with T2DM are generally twice as often affected by sexual problems compared to persons without T2DM [3]. Men most frequently report erectile dysfunction (ED), with prevalence rates ranging from 36 to 84 % [4–9], followed by ejaculation disorders and hypoactive sexual desire disorder, 40 and 25 % respectively [7, 10]. In addition, ED is prevalent in newly diagnosed patients and is often comorbid with other sexual dysfunctions [11]. Among women, hypoactive sexual desire disorder and lubrication problems are common with prevalences of 46–82 % and 38–70 % respectively [12–15]. Women with T2DM also report arousal disorders (68 %), orgasmic disorders (38–84 %), and dyspareunia (43–46 %) [12–15].

Sexual dysfunction negatively affects the quality of life of patients with T2DM. Patients with diabetes rate their sex life as less satisfying than persons without diabetes [13, 14, 16]. Men with T2DM with ED report significantly worse emotional and psychological well-being, and more diabetes-related distress [17–19]. Even though less is known how sexual dysfunction affects the quality of life of women with T2DM, research in women with type 1 diabetes suggests a negative effect on quality of life as well [20]. Altogether, the high prevalence and negative effects of sexual dysfunction in patients with T2DM warrant clinical attention.

In the Netherlands, diabetes care is organised in primary care. Patients with T2DM generally have three-monthly control visits with the practice nurse and a yearly consultation with their general practitioner (GP). According to the Dutch Society of General Practitioners (NHG) diabetes treatment guideline, sexual issues should be addressed during this yearly appointment with the GP [21]. The GP should explicitly inquire whether the patient experiences sexual problems, including ED, loss of sexual desire, and decreased vaginal lubrication. In addition, the GP should discuss possible treatment options, such as medication adjustment [21]. Nevertheless these guidelines, sexual problems remain to be frequently neglected in diabetes care [22, 23].

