## Methods

### Design and setting

This study is a cluster RCT, registered at the Dutch Trial Registry (NTR4807). The study protocol was peer-reviewed by the Dutch Diabetes Research Foundation. The study was approved by the Medical Ethics Committee of the VU University Medical Centre in Amsterdam, The Netherlands.

The study will be conducted in primary care practices in the western part of the Netherlands: the West-Friesland region, the Zaanstreek-Waterland region, and Amsterdam area. Both urban and rurally located general practices will be included. Randomisation takes place at the level of general practice. Eligible patients will either be included in the intervention or control group: structured sexual counselling based on the PLISSIT model versus unstructured sexual counselling (usual care).

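### The sensitivity analysis restricted to patients with a GP appointment compares groups selected differently by arm, so it neither tests the intention-to-treat result nor isolates PLISSIT

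*Protocol article*

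**What the plan says.** The Analyses section makes intention-to-treat the main analysis, by linear and logistic multilevel regression. It then gives a reason for one further analysis, "Given that not every patient in the control group will have had an appointment with their GP", and states that "a sensitivity analysis will be conducted to compare patients who had an appointment with their GP in the intervention versus control group".

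The Recruitment section (text after Figure 2) shows how an appointment comes about in each arm:

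- Intervention: after the leaflet, "the practice nurse will subsequently make an appointment with the GP for each patient to talk about sexual problems".
- Control: "Practice nurses in the control group do not automatically make an appointment with the GP for every patient". The nurse instead asks "whether the information leaflet was of sufficient help or whether the patient would like to have an appointment with his/her GP nevertheless".

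The Methods/Design part of the abstract describes the control rule in the same way: usual care from the GP goes to those who ask for it because the leaflet was not enough.

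**The concern.** Having an appointment is determined after randomisation, and by a different mechanism in each arm. In the intervention arm it follows from routine booking. In the control arm it follows from the patient's reaction to the leaflet. Control attenders are therefore a filtered group. They may have worse or more persistent problems, or they may be more motivated to do something about them. Intervention attenders have passed no such filter, apart from any failure to keep a booked appointment.

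This matters because it is the only analysis in the article that sets PLISSIT counselling against ordinary GP counselling among patients who were actually counselled. The intention-to-treat contrast answers another question: automatic appointment with a trained GP against optional appointment with usual care. The attender comparison could show a difference when PLISSIT does nothing, or hide one when it works. Called a sensitivity analysis, it also invites use as a robustness check on the intention-to-treat result, which it is not, because it targets a different contrast in a different population.

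**Working it through.** **1. The plan's own figures (Sample size section).** For 10% versus 35%, two-sided alpha 0.05 and power 0.90, the two-proportion formula gives 57 per group without continuity correction and 65 with it, so the stated 65 is reproduced. The design effect is 1 + (6 − 1) × 0.05 = 1.25. Then 130 × 1.25 = 162.5, and 162.5 × 1.20 = 195, as stated. The planned effect is 25 percentage points. On a probit scale it is 1.28 − 0.39 ≈ 0.90 SD.

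**2. Who enters the comparison.**

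| | Intervention | Control |
|---|---|---|
| Wish to talk to the GP at screening | required | required |
| Baseline questionnaire | before leaflet | before leaflet |
| Leaflet | yes | yes |
| Appointment | booked for each patient | only if still wanted after the leaflet |

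The arms are alike down to the leaflet and part at the last row, which is the row the analysis selects on.

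**3. Size on a continuous outcome, no PLISSIT effect.** These are assumptions, not document figures: a fraction p of controls request an appointment; requesting correlates ρ = 0.3 to 0.5 with severity; baseline and follow-up correlate 0.6; all intervention patients attend. With z the normal quantile at p, requesters are worse at baseline by ρ × φ(z)/p, and at follow-up by 0.6 times that.

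| p | φ(z)/p | Follow-up shift, ρ = 0.3 | Follow-up shift, ρ = 0.5 |
|---|---|---|---|
| 0.30 | 1.159 | 0.21 SD | 0.35 SD |
| 0.50 | 0.798 | 0.14 SD | 0.24 SD |
| 0.70 | 0.497 | 0.09 SD | 0.15 SD |
| 0.80 | 0.350 | 0.06 SD | 0.11 SD |

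The false difference is thus 0.14 to 0.35 SD at 30–50% uptake and 0.06 to 0.15 SD at 70–80%. Against the planned effect of about 0.90 SD that is 16–39% and 7–17%. It favours the intervention if severity drives requests. If motivation drives them, the sign can reverse.

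**4. Size on a binary outcome, no PLISSIT effect.** Let control attenders have response odds OR times those of control non-attenders, with the same overall response in both arms (OR and uptake assumed). The false difference, intervention minus control, in points:

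| Overall response | Control uptake | OR 0.33 | OR 3 |
|---|---|---|---|
| 10% | 30% | +5.5 | −7.7 |
| 10% | 50% | +4.6 | −4.6 |
| 10% | 70% | +3.3 | −2.4 |
| 35% | 30% | +15.8 | −18.0 |

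**5. Loss of precision.** With 200 recruited, 200 × 0.8 / 1.25 / 2 = 64 effective patients per arm, and power for 10% versus 35% is 93%. With control uptake of 70%, 50% or 30% it falls to 87%, 78% or 58%. These values keep the design effect at 1.25. The smaller control clusters would lower it somewhat, so they are slightly pessimistic.

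**The case against.** The strongest reply is that this is a supplementary analysis. Intention-to-treat is the main one, nothing in the sample size depends on the attender comparison, and the article never says that it isolates PLISSIT. That stands, and it limits the weight of the point.

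A second reply is that the shift in step 3 arises wholly through baseline severity, which is measured before the leaflet is handed over. Under those same assumptions, adjusting for baseline would remove it, and covariates may be fixed in an analysis plan that is not shown. This also stands for selection on measured severity. It does not cover the reaction to the leaflet itself, or motivation, where these are not captured by the baseline scores.

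Third, every participant said at screening that they would like to talk to the GP, so control uptake may be high. That narrows the selection but does not remove it, because controls are filtered a second time after the leaflet.

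Some stronger readings are tempting but not supported:

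- *That most controls receive no counselling.* The article says only that not all of them will have an appointment.
- *That a yearly GP visit would count as an appointment.* The yearly consultation in Background is general context. Recruitment describes an appointment about sexual problems, and Process analysis asks every patient at 3 and 12 months about such a conversation.
- *That the main contrast is misdescribed.* Design and setting speaks briefly of structured against unstructured counselling, but the abstract and Recruitment set out the automatic and the on-request appointment plainly.

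**Conclusion.** The point holds for the sensitivity analysis alone. Its two groups are formed after randomisation by different rules, so a difference between them cannot be attributed to PLISSIT, and agreement with the main result would not show that result to be robust. A reader might infer that the trial's main conclusion is compromised. It is not, because the intention-to-treat comparison keeps the randomised groups. This should be fixed, but it is not a fatal flaw.

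The direction of bias is unknown. Its size rests on control uptake and on the prognostic weight of a request, neither of which the article gives. On the stated assumptions it runs from about 0.06 to 0.35 SD before baseline adjustment, or from a few points up to about 18 points on a response scale, against a planned 25 points. These ranges show that the bias need not be negligible. They are not estimates of what will occur.

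**What to change.** **Preferred.** Have nurses in both arms ask and record the same leaflet question at the same moment, before the intervention appointment is booked. Booking stays as planned in both arms. Replace the attender comparison by one between the patients in each arm who answered that they would like an appointment, adjusted for baseline scores. The subset is then defined by the same question in both arms.

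The cost is one recorded item, a small extra exchange in intervention practices and a sentence in the Analyses section. The nurse asking knows the allocation, so answers could still be influenced by arm. Patients are unaware of it, which helps. The subset is also smaller than the full sample, so power is lower. The item has to be in place during recruitment, because intervention patients' answers cannot be recovered afterwards.

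**If the question cannot be added.** Keep the attender comparison only as an exploratory analysis, explicitly labelled non-randomised. Identify attenders by the Process analysis item on a conversation with the GP about sexual problems. Adjust for, or weight on, the baseline questionnaire scores, and report the baseline comparability of the two attender groups. Do not present the result as a robustness check on intention-to-treat or as evidence for PLISSIT over usual GP counselling. This costs wording only.
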